**Figure 2. F2:**
[figure not shown]
Professional Readiness in Diversity and Equity (PRIDE) scale statistical analysis plan for scale evaluation. CFI: comparative fit index; GRM: graded response model; ML: maximum likelihood; RMSEA: root mean square error of approximation; SRMR: standardized root mean square residual; TIFs: test information functions; TLI: Tucker-Lewis index.

Missing data will be assessed prior to all analyses. For the United States sample, participants were required to fill all survey items, with branching (skip) logic implemented for respondents who did not currently engage in clinical practice. For the European sample, participants were permitted to skip responses for demographics only. We concatenated all complete and partial responses and participants with more than 10% of items missing will be excluded. For the remaining participants, missing values in the CFA framework will be handled using full information maximum likelihood estimation [42,43]. Descriptive and known-groups validity analyses will use pairwise deletion. The proportion and pattern of missing data will be reported, and missing completely at random test by Little will be used to evaluate the missing data mechanism.

As the use of convenience sampling (eg, through professional networks, institutional contacts, and online platforms) can introduce selection bias, to evaluate sample representativeness, the demographic profile of respondents in each country will be compared against available national health care workforce statistics. To ensure reproducibility of all data management and analytic procedures, a fixed random seed will be set prior to all data manipulation steps (seed=123,456). Prior to splitting, early respondents will be identified within each country as the first 25% of participants by enrollment order, to allow subsequent assessment of early responder bias. The sample will then be randomly split 50/50 within each country, with participant order randomized using a uniform random variable to remove any time- or motivation-related ordering effects, yielding Split A as the estimation subsample for EFA and Split B as the holdout subsample for CFA. Balance between the 2 subsamples will be verified for country distribution, LGBTQI+ identity status, and the proportion of early respondents, both overall and within each country, using cross-tabulations and Fisher exact tests. Limitations associated with convenience sampling, including potential volunteer bias and overrepresentation of professionals with prior interest in LGBTQI+ inclusive practice, will be explicitly acknowledged and considered in interpreting the generalizability of the validation findings.

#### EFA and CFA

EFA will be conducted to examine the underlying dimensional structure of the PRIDE scale and to inform item retention. As an initial parametric approach, EFA will be performed using principal component analysis (PCA) with varimax (orthogonal) rotation to obtain a simple and interpretable factor solution. Prior to extraction, the suitability of the data for factor analysis will be assessed (eg, inspection of the correlation matrix and standard measures of sampling adequacy). The number of factors to retain will be determined using the Kaiser criterion (eigenvalues ≥1) in conjunction with visual inspection of the scree plot to identify the point of inflection. Items will be evaluated based on their pattern of loadings, and only items with primary factor loadings ≥0.40 will be considered for inclusion. Items showing substantial cross-loadings (eg, ≥0.30 on more than 1 factor) or weak or unstable loadings will be reviewed for removal or revision, with decisions guided by both statistical evidence and conceptual coherence with the intended constructs. Given the ordinal nature of Likert-type responses, a complementary nonparametric ordinal approach will also be implemented. Specifically, a polychoric correlation matrix will be estimated and subjected to factor analysis with varimax rotation, applying the same factor-retention rules (eigenvalues ≥1 and scree plot) and item-selection criteria (primary loading ≥0.40, limited cross-loading). Consistency of the factor structure across the PCA-based and polychoric-based solutions will be examined to strengthen inferences regarding dimensionality and to ensure that the final factor model is robust to distributional assumptions. We acknowledge that PCA is technically a data-reduction technique that accounts for total item variance rather than modeling shared latent variance exclusively, and therefore does not constitute a latent variable model in the strict sense [30,44]. Its use here is pragmatic, consistent with its established role as an initial item-selection tool at the exploratory stage. The robustness of the dimensional solution will be evaluated formally through the planned cross-validation against the polychoric-based factor solution and, most importantly, through the subsequent CFA with maximum likelihood estimation, which will constitute the primary evidence for the latent structure of the PRIDE Scale.

CFA will be used to confirm the factor structure identified in the EFA. Model fit will be evaluated using the following indices: chi-square statistic, comparative fit index (CFI), root mean square error of approximation (RMSEA), standardized root mean square residual (SRMR), Tucker-Lewis index, Akaike information criterion, and Bayesian information criterion will be used following cutoff recommendations by Hu and Bentler [45,46].

To establish the cross-cultural and cross-demographic equivalence of the PRIDE Scale, formal measurement invariance testing will be conducted using multigroup confirmatory factor analysis. Following the sequential approach recommended by Vandenberg and Lance [47] and Putnick and Bornstein [48], configural invariance (same factor structure across groups), metric invariance (equal factor loadings), and scalar invariance (equal item intercepts) will be tested sequentially across two sets of planned comparisons: (1) Italian-speaking and English-speaking (United Kingdom and United States combined) subsamples, to establish cross-linguistic and cross-national measurement equivalence; and (2) LGBTQI+ and cisgender heterosexual participants, to evaluate whether the scale functions equivalently across groups that differ in sexual orientation and gender identity; a particularly important consideration given the nature of the construct being measured. Model comparisons will be evaluated using the chi-square difference test and changes in CFI (ΔCFI ≤−0.010) and RMSEA (ΔRMSEA ≤0.015) as criteria for invariance [49]. Additional subgroup analyses will be conducted to assess the potential influence of professional background (student vs trained practitioner) and gender on the validity of the CFA solution [50]. Where measurement invariance testing reveals a failure of scalar invariance for specific items, differential item functioning (DIF) analyses will be conducted as a planned follow-up to identify items performing differently across subgroups. DIF will be evaluated using ordinal logistic regression, which enables the detection of both uniform and nonuniform DIF for polytomous Likert-type items. Items exhibiting significant and practically meaningful DIF will be flagged for review during subsequent scale refinement.

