## Methods

### Scale Development and Measures

The PRIDE Scale included 39 new test items examining LGBTQI+ health care knowledge, awareness, attitudes, skills, and the work environment,. Development of these items was iterative and generated through literature reviews, expert consultation, and adaptation from existing scales. The Delphi method was used to select the most relevant items via iterative rounds of feedback from an expert panel. The first step was to identify and recruit a diverse group of international experts with relevant experience in LGBTQI+ health care, psychometric scale development, and clinical competence. These experts included health professionals (mostly physicians and psychologists), LGBTQI+ health advocates, clinicians, researchers, public health professionals with expertise in biostatistics and epidemiology, and educators. In total, the panel was comprised of 12 members. There were 3 Delphi rounds. In the first round of item generation, experts on the study team developed a broad number of items (100) both from the existing literature and newly formed items, which were then randomly listed and presented to the expert panel. Experts were asked to evaluate each item based on its relevance, clarity, and its potential importance for measuring LGBTQI+ related competencies among health care professionals. Experts could also comment on each item and suggest new or adapted items. After the first round, responses were scored for relevance and ordered accordingly. Quantitative consensus was defined a priori as a threshold of ≥75% and a median rating of ≥4 on a 5-point scale indicating an item as important or very important. These thresholds align with accepted Delphi standards and ensure that retained items reflect high agreement and rating stability. Based on the scoring (1-100), 39 items that showed strong consensus for inclusion were retained. These items are measured on a 5-point Likert-style scale that ranges from 1 (strongly disagree) to 5 (strongly agree).

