### Study Population and Sample

The study population consisted of health professionals, including students or health professionals-in-training, such as physicians, nurses, and other allied health professionals (eg, podiatrists, occupational therapists, physiotherapists, and mental health professionals) working in Italy, the United Kingdom, and the United States, with respondents able to complete the survey in English or Italian, depending on the country. The goal was to have a norming sample of international health care professionals including those in-training.

Sample size was calculated considering the 2 main statistical techniques to be used in the analysis: exploratory factor analysis (EFA) and confirmatory factor analysis (CFA). Based on the literature, as a rule of thumb (item-to-participant ratio), 5 to 10 participants per item are required [29-32]. For the 39-item PRIDE scale, this would translate to a minimum of 195 participants (5 participants per item) and a preferred sample size of 390 participants (10 participants per item). However, as we are planning an EFA and CFA, a total of approximately 700 participants is planned. For test-retest reliability, based on Walter et al [33], and assuming a null intraclass correlation coefficient of 0.40, an expected intraclass correlation coefficient of 0.70, 2 administrations of the scale, a significance level (α) of 0.05, and a power (1–β) of 0.80, a sample size of 62 is required.

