#### Reliability Estimates and Test-Retest Reliability

Internal consistency reliability for the PRIDE scale will be evaluated within each sample (United States and Europe) and reported for each subscale, and for the total scale only if a defensible higher order or general-factor model supports total scoring. Reliability will be quantified using Cronbach α and, for ordinal Likert-type items, ordinal alpha (α_ord) computed from a polychoric correlation matrix. In addition, McDonald omega (ω) will be estimated for each monotone or unidimensional subscale using a congeneric factor model (allowing heterogeneous item loadings) and will be treated as the primary model-based estimate; where relevant, omega estimates derived under an ordinal framework (polychoric correlations or appropriate ordinal estimators) will be reported. Item-total correlations will be examined to assess the contribution of individual items to subscale reliability, and items with low item-total correlation (eg, <0.30) will be flagged for potential removal in conjunction with evidence from MSA, CFA (factor loadings or model fit), and IRT GRM outputs (discrimination, thresholds, and information), in accordance with the prespecified item selection rules. Test-retest reliability correlations will establish temporary (2-wk) stability of the PRIDE Scale using the blinded combined United States and European samples pooled. The test-retest sample size power calculation suggested an ideal sample size of 62 for this reliability test.

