## Results

Data collection funded in May 2023 and was conducted from October 2024 to December 2025, with a total of 1339 eligible participants who completed the survey. Data cleaning and preparation are underway, and data analysis will take place in Summer 2026, with the first results paper expected to be submitted in Autumn 2026.

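### The number of factors rests on eigenvalues ≥1 plus a scree reading with no tie-break, and both exploratory solutions share that rule and varimax, so the result can turn on a subjective judgement

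*Protocol article*

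**What the plan says.** All references are to the protocol article.

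- **Extraction and rotation** (EFA and CFA): the first exploratory solution is "principal component analysis (PCA) with varimax (orthogonal) rotation to obtain a simple and interpretable factor solution".
- **Number of factors** (same section): "The number of factors to retain will be determined using the Kaiser criterion (eigenvalues ≥1) in conjunction with visual inspection of the scree plot". No precedence is given if the two parts point to different numbers.
- **Second solution** (same section): a polychoric matrix is factor-analysed, again with varimax, "applying the same factor-retention rules (eigenvalues ≥1 and scree plot"). The consistency of the two solutions is then examined.
- **Item rules** (same section): a primary loading of at least 0.40 is needed. Items loading 0.30 or more on more than one factor are reviewed for removal or revision.
- **Confirmation** (same section): the CFA on Split B confirms the structure found in the EFA and is the primary evidence for the latent structure. No rival number of factors is named.
- **Total score** (Reliability Estimates and Test-Retest Reliability): reliability is reported "for the total scale only if a defensible higher order or general-factor model supports total scoring".

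The article defends PCA as a pragmatic choice. It offers no argument for the eigenvalue rule, and supports varimax only as simple and interpretable.

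**The concern.** Even when no factor exists, sampling error pushes many eigenvalues of a correlation matrix above 1. The number that exceed 1 grows with the number of items, so a fixed cut-off at 1 is a weak rule for 39 items. The scree plot is the only counterweight, and it is read by eye. Two competent analysts could retain different numbers of factors and both would have followed the plan.

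The choice has consequences downstream. Surplus components split real subscales and spread loadings, which triggers the 0.30 cross-loading review. The Mokken screening uses the EFA results, and the CFA tests the structure passed to it. Comparing the PCA with the polychoric solution mainly tests robustness to the ordinal response format. It is a weak check on the retention rule and rotation, because both solutions share them.

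Varimax fixes the factor correlations at zero. Knowledge, awareness, attitudes and skills are plausibly correlated facets of competence, and the case for a total score depends on how strongly they correlate. Neither exploratory solution would report this.

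**Working it through.** **1. Inputs from the article.**
- Items: 39. "For the 39-item PRIDE scale, this would translate to a minimum of 195 participants (5 participants per item"). The item-ratio figures reproduce: 39 × 5 = 195 and 39 × 10 = 390. The article states no expected number of factors, so there is no such figure to reproduce.
- Response format: "These items are measured on a 5-point Likert-style scale that ranges from 1 (strongly disagree) to 5 (strongly agree").
- Sample: "a total of approximately 700 participants is planned", so 700 / 2 = 350 in the EFA half. Achieved: "with a total of 1339 eligible participants who completed the survey", so 1339 / 2 ≈ 669, before exclusions for missing items.

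**2. Assumptions not in the article.** Five true factors, matching the five content areas listed under Scale Development and Measures; a common factor correlation r; the loading range; and the response skew. No item has a true cross-loading.

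**3. Model and rules.** Item i belongs to factor g(i). Its latent response is x = λ·F + √(1 − λ²)·e, cut into five categories.
- Eigenvalue rule: K = number of eigenvalues ≥ 1.
- Parallel analysis: keep leading eigenvalues while each exceeds the 95th percentile of the same-ranked eigenvalue from random data of the same size.
- Flag: an item with absolute loading ≥ 0.30 on more than one component after PCA and varimax.

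These were applied to Pearson correlations, with 100 to 200 simulated data sets per scenario. The polychoric solution was not simulated.

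**4. Noise only, 39 items.** Eigenvalues ≥ 1 average 18.2 at N = 350 and 18.6 at N = 669.

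**5. Main scenario: loadings 0.45–0.75, r = 0.5.**

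| N and skew | Kept by eigenvalue ≥ 1 | Items flagged (of 39) at that number |
|---|---|---|
| 669, skewed (cuts −2.2, −1.6, −1.0, −0.2) | 7.7 to 7.9 | 7 to 7.6 |
| 669, symmetric | 5.8 to 5.9 | 2.4 |
| 350, skewed | 10.1 | 12 |

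For the skewed items at N = 669, parallel analysis keeps 5.0, and a five-factor varimax solution flags almost none.

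**6. Dependence on loadings.** Milder skew (cuts −1.8, −1.1, −0.3, 0.7); ranges run over r = 0 to 0.7. Flagged items are the simulated percentage × 39, for example 0.128 × 39 = 5.0.

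| Loadings | K at N = 350 | K at N = 669 | Share with K > 5, N = 669 | Items flagged, N = 669 |
|---|---|---|---|---|
| 0.4–0.6 | 11.3–11.8 | 9.2–9.5 | 100% | 10.6–11.4 |
| 0.4–0.8 | 8.4–8.8 | 6.5–6.8 | 93–98% | 4.4–5.0 |
| 0.5–0.7 | 7.8–8.0 | about 5.6 | 50–57% | 1.8–2.5 |
| 0.6–0.8 | 5.1 | 5.0 | 0% | 0–0.3 |

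**7. The scree part.** As a crude proxy for the inflection, take the largest gap after the first eigenvalue. In the skewed main scenario it falls at five factors in 100% of data sets at N = 669, r = 0.5; in 73% to 75% at N = 669, r = 0.7; and in 84% at N = 350, r = 0.5.

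**8. Rotation alone.** With the correct five factors, r = 0.7 and N = 669, varimax flags about 1.4 items and an oblique rotation about 0.3. The difference is 1.4 − 0.3 = 1.1 items.

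**9. The proposed replacement.** In the runs of step 6, parallel analysis keeps 4.9 to 5.0 factors for r up to 0.5 at both sample sizes. At r = 0.7 it keeps too few: about 4.4 of 5 at N = 669 and about 3 at N = 350 in the skewed main scenario.

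**The case against.** The strongest reply is that the plan does not use eigenvalues ≥ 1 alone. Step 7 shows that a reasonable scree reading usually recovers the right number, and the steps 5 and 6 counts ignore it. This stands: a reader might infer that the plan will over-extract, and the article does not support that. What remains is that the two parts would then disagree (8 against 5, for example) and the plan does not say which prevails.

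Second, the true number of factors, loadings, correlations and skew are all assumed. With uniformly high loadings at the achieved sample size the problem vanishes. This also stands. Against it, the item rule admits loadings from 0.40, these are new items, and the article itself expects non-normal distributions and an over-representation of supportive professionals.

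Third, the polychoric solution is a factor analysis, and the article does not say which matrix supplies its eigenvalues. On a reduced matrix, noise gives none ≥ 1 and the skewed main scenario gives about 4.3 (Pearson-based), so the two solutions could disagree and reveal the problem. The comparison is therefore a weak safeguard, not a worthless one. No rule says what follows from a disagreement.

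Fourth, flagged items are reviewed, not dropped automatically, and Mokken, graded response and content criteria also apply. That softens the consequence. The holdout CFA helps less than it seems. If one factor is split in two and factors may correlate, the true model is the special case with correlation 1, so good fit need not expose the split.

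Finally, a reader might infer that varimax contradicts the plan's own higher-order scoring. It does not: that model is conditional, and orthogonal rotation in the EFA does not bar correlated or second-order factors in the CFA. There is a tension only.

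**Conclusion.** The point holds as a weakness in a stated rule, not as a demonstrated error. The number of factors depends on a visual judgement with no tie-break, paired with a criterion that tends to over-extract for 39 items when loadings are moderate or mixed.

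The size is conditional. With five factors at r = 0.5, loadings 0.45–0.75 and N = 669, following the eigenvalue count gives about 6 to 8 factors and flags about 2 to 8 of 39 sound items, depending on skew. With loadings of 0.6–0.8 there is essentially no excess at that sample size. Had only the planned 700 been recruited, the excess would have been larger.

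The effect of varimax alone is small, about one item at r = 0.7 and N = 669. Its main drawback is that it supplies no factor correlations to inform a total score. All sizes rest on the assumptions in step 2 of the working and on Pearson correlations.

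**What to change.** 1. Set the number of factors by parallel analysis (95th percentile) on the polychoric matrix, with MAP or the scree plot as a second check.
2. State the tie-break: if the two disagree, carry each candidate number forward and compare them in the Split B CFA, together with a second-order model.
3. Make common-factor extraction on the polychoric matrix with oblique rotation (oblimin or promax) the primary solution. Apply the 0.40 and 0.30 rules to the pattern matrix and report the factor correlations.
4. Keep PCA with varimax as a sensitivity analysis.

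The cost is a few lines of code and wording and a little more analysis; no new data are needed. The drawback is that parallel analysis alone can under-extract when factors correlate about 0.7, which is why the tie-break is part of the fix. The Abstract says analysis has started, while the Results section places it in Summer 2026. The change should be dated before the Split A eigenvalues are inspected, or reported as a later change if they already have been.

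### The check of robustness to distribution changes extraction and correlation type together, so its result on item selection cannot be attributed to distribution

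*Protocol article*

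**What the plan says.** Everything on this point stands in the protocol article, Statistical Analysis, subsection EFA and CFA.

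- First solution, labelled parametric: "EFA will be performed using principal component analysis (PCA) with varimax (orthogonal) rotation". The matrix is not named. I take it to be the Pearson matrix of the item scores.
- Second solution, labelled nonparametric and ordinal: "a polychoric correlation matrix will be estimated and subjected to factor analysis with varimax rotation". The extraction is not named further. Its cutoffs are carried over unchanged from the first solution: eigenvalues of at least 1 read together with the scree, a primary loading of at least 0.40, and little cross-loading.
- Purpose of comparing them: "Consistency of the factor structure across the PCA-based and polychoric-based solutions will be examined", partly "to ensure that the final factor model is robust to distributional assumptions".
- Caveat on the first solution: it "accounts for total item variance rather than modeling shared latent variance exclusively", and its use is described as pragmatic.
- Reliance: "The robustness of the dimensional solution will be evaluated formally through the planned cross-validation against the polychoric-based factor solution". The same sentence ranks the later maximum likelihood CFA above this comparison, as the analysis "which will constitute the primary evidence for the latent structure of the PRIDE Scale".

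The Analytical Methods subsection expects the items to be nonnormal. The EFA uses one half of the sample and the CFA the other half.

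**The concern.** The question put to the comparison is whether the result changes once the items are treated as ordinal. To answer it, only the correlation type should change. Here the extraction changes as well, from components (total variance) to factors (shared variance), while the numeric cutoffs stay the same. The plan describes no solution that changes one of the two alone.

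This matters in both directions. If the two item lists differ, the difference may come from extraction and say nothing about distribution. If they match, two effects of opposite sign may have offset each other. A loading of 0.40 is also a softer hurdle under PCA than under a common-factor model, so the shared rule does not screen items equally in the two solutions. What is at stake is the screening of borderline items and the published statement that the structure is robust to distributional assumptions.

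**Working it through.** The plan gives no figure to reproduce here, so the check is analytic and then numerical.

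**Inputs from the protocol article:** 39 items on a 5-point scale; loading cutoff 0.40; 1339 completers split in half, so 1339 / 2 = 669.5, about 670 for the EFA before exclusions.

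**Assumptions, not in the article:** five factors with simple structure, factor correlation 0.3 unless stated, and a range of true loadings.

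**Step 1. Why PCA loadings are higher.** Take one factor with p items, all of true loading λ, and exactly normal data. The first eigenvalue of the full correlation matrix is 1 + (p − 1)λ². Each PCA loading is the square root of that divided by p:

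PCA loading = √(λ² + (1 − λ²)/p).

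A common-factor extraction returns λ. With 39 items on five factors there are about p = 8 per factor:

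- λ = 0.60: √(0.36 + 0.64/8) = √0.44 = 0.66
- λ = 0.35: √(0.1225 + 0.8775/8) = √0.2322 = 0.48
- λ = 0.20: √(0.04 + 0.96/8) = √0.16 = 0.40

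So in a homogeneous set the PCA cutoff of 0.40 is met at a true loading of 0.20. In mixed sets the gap varies by item but keeps its direction on average.

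**Step 2. Population matrices, exactly normal items.** Pearson and polychoric correlations coincide, so only extraction differs (PCA against iterated principal axis, both varimax, five factors).

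| True loadings, factor correlation | Mean primary loading, PCA / factor | Items at ≥0.40, PCA / factor |
|---|---|---|
| 0.3-0.7, 0 | 0.586 / 0.500 | 38 / 29 |
| 0.3-0.8, 0.3 | 0.610 / 0.531 | 38 / 30 |
| 0.4-0.8, 0.3 | 0.648 / 0.580 | 39 / 37 |
| 0.5-0.8, 0.3 | 0.686 / 0.628 | 39 / 39 |

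**Step 3. Simulated samples, n = 670, five factors fixed.** The entries are the mean number of the 39 items classified differently at 0.40 (200 samples per row). The last column changes only the correlation type; for normal items it is zero by construction.

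| Items | True loadings | Planned contrast | Factor analysis on both matrices |
|---|---|---|---|
| Normal | 0.3-0.8 | 7.0 | 0 |
| Normal | 0.4-0.8 | 2.4 | 0 |
| Symmetric 5-point | 0.3-0.8 | 6.5 | 1.5 |
| Symmetric 5-point | 0.4-0.8 | 2.4 | 1.4 |
| Skewed 5-point | 0.3-0.8 | 4.7 | 4.0 |
| Skewed 5-point | 0.4-0.8 | 2.2 | 4.3 |

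Further runs with other arrangements of loadings and thresholds gave, on normal items, 6.8 at loadings 0.35-0.70, up to 3.7 at 0.4-0.8, and under 0.1 at 0.5-0.8. Hence about 7, about 3 and almost none.

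**Step 4. Masking.** In the last row the planned contrast shows fewer differences than the correlation type alone produces (2.2 against 4.3). Other runs of that setting gave 1.8 against 3.6 and 2.8 against 3.2. PCA raises loadings while Pearson correlations on skewed categories lower them, so the two partly offset. At 0.3-0.8 the planned contrast was the larger (4.7 against 4.0), so masking is possible but not general.

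**Step 5. What does not change.** With five factors fixed, both solutions grouped the items into the same factors in the settings checked (0.35-0.70, 0.4-0.8, 0.5-0.8 and all 0.6). The number of factors differed in 0-1% of samples by a largest-gap proxy for the scree, and in at most 9% when eigenvalues ≥1 were counted on the unreduced matrix in both solutions.

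**The case against.** The strongest reply is that the plan compares factor structure, not item lists, and that the structure agrees: items go to the same factors and a scree reading gives the same count. That stands, and it confines the point to item selection at the loading cutoff.

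A reader might infer that the two solutions will nearly always retain different numbers of factors. Disagreement does approach 100% of samples in several settings, but only if eigenvalues ≥1 are counted on the reduced matrix for the factor analysis and the scree plot is ignored. The article does not specify the reduced matrix, and it pairs the eigenvalue rule with the scree in both solutions.

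A reader might also infer that weak items will end up in the scale. The article does not support that. Meeting 0.40 only makes an item a candidate; Mokken analysis, graded response models and item-total correlations follow, and the holdout CFA is named as the primary evidence. That limits the consequence without removing it, because the CFA tests the structure passed on from this step and is planned with maximum likelihood.

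The caveat about PCA admits the difference in extraction but does not separate it from distribution. If the polychoric analysis in fact extracted components, the confounding would vanish, but the article contrasts PCA with a polychoric-based factor solution, so that is not the natural reading.

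Which item list goes forward after disagreement is detail that an article may leave to the full plan. Calling a comparison within one half-sample cross-validation is loose terminology, since the holdout half has that role. Neither is part of this point.

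**Conclusion.** The point holds in a limited form. As described, the comparison cannot answer the question assigned to it, because two things change at once under identical cutoffs. That conclusion rests on the text alone.

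Its size depends on the true loadings, which are unknown before analysis. On exactly normal data, with five factors correlated 0.3, five factors fixed and n = 670, about 7 of 39 items are classified differently for loadings of 0.35-0.70, about 3 for 0.4-0.8, and almost none if all are 0.5 or more. With skewed items, which the article expects, apparent agreement can hide a distributional effect. The consequence reaches the screening of borderline items and the wording of the robustness claim. It does not extend to the dimensional structure as such or to the validity of the holdout CFA.

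**What to change.** In the EFA and CFA subsection, name one common-factor extraction (for example principal axis or minimum residual) and run it with the same retention rule and rotation on both the Pearson and the polychoric matrix. Base the statement about distributional robustness on that contrast only. Apply the 0.40 primary-loading and 0.30 cross-loading rules to the polychoric common-factor solution, and keep PCA as a descriptive first look.

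The cost is a wording change and one extra run, the common-factor analysis of the Pearson matrix; the polychoric factor analysis is already planned. The downside is that a few borderline items that pass under PCA may no longer reach 0.40. The change should be fixed before the loadings are examined.
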